# Study Design and Procedures

The study will be conducted according to the following design and procedures in the flowchat:

Exclusion by no qualified sample

Exclusion by rectified diagnosis as non-infectious diseases or non-bacterial infections

Specimen collection and evaluation

men

ollection and evaluation

Consecutive suspected LRTI patients according to inclusion criteria

Informed Consent Form Signed

Clinical information input

Statistical analysis

1st day anticoagulated blood

1st day

sputum

1st day

sputum

3r day

sputum

2nd day

sputum

anticoagulated blood (at least 10days late)

)

LAMP & Culture in core lab

Culture in local hospital

Serological test in core lab

# Statistical Plan

## Sample Size

Sample size of this study will not be accurately estimated because lack of accurate positive rate for each evaluated pathogen caused infection in LRTI patients. We estimate the positive rates range 5-15%, and the sensitivity of the index qLAMP test is 90- 95%, then 400-3000 eligible patients are needed for statistical analysis. We finally plan to enroll 1500 eligible patients..

## Statistical Methods

Using SPSS version 17.0, the data were summarized in a receiver operating characteristic (ROC) curve to determine the diagnostic efficacy, the area under the curve (AUC) and its 95% confidence interval (95% CI) were calculated as a measure for the discriminative efficacy of the index test.

R software will be used to construct statistical model to explore to relationship between the result of both tests, and calculate cut-offs if necessary.

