# Study Summary

| Title | Prospective, multi-center, clinical study of quantitative LAMP vs. routine culture/serological test for etiologic diagnosis in LRTI patients |
| --- | --- |
| Short Title | Etiologic Diagnosis of LRTI via LAMP |
| Protocol Number | 00001384 |
| Study design | Consecutive LRTI patients are planed to be enrolled in multi-centers, sputum samples from eligible subjects are planed to be applied to parallel tests of qLAMP and culture/serological test, the results and accuracy of both tests are to be compared and determined statistically. |
| Study Duration | Dec 2007-Dec 2008 |
| Study Center(s) | 21 centers—21 tertiary hospitals over 14 provinces of P. R. China agreed to participate. |
| Objectives | Evaluate the accuracy of qLAMP in etiology diagnosis of LRTI patients. |
| Number of Subjects | About 3000 LRTI patients |
| Diagnosis and Main Inclusion Criteria | Patients were suspected to have bacterial LRTI with typical diagnoses of pneumonia or bronchitis based on chest X-ray, as well as clinical symptoms and simple laboratory signs. |
| The evaluated test | Quantitative LAMP of 11 common bacteria in LRTI subjects. |
| Reference test | Routine bacterial culture/serological test |
| Statistical Methodology | Using SPSS version 17.0, the data were summarized in a receiver operating characteristic (ROC) curve to determine the diagnostic efficacy, the area under the curve (AUC) and its 95% confidence interval (95% CI) were calculated as a measure for the discriminative efficacy of the index test.  R software will be used to construct statistical model to explore to relationship between the result of both tests, and calculate cut-offs if necessary. |

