## Subject Recruitment and Screening

Potential bacterial LRTI patients were consecutively enrolled from 21 tertiary hospitals over 14 provinces in People’s Republic of China as the inclusion criteria, then samples will be collected to quality evaluation. Subjects with qualified samples will be applied to qLAMP and routine culture/serological test assay. Subjects adapt to exclusion criteria after informative diagnosis will be excluded.

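### Section 5.2 makes no allowance for the 21 hospitals in the AUC confidence interval, which would be too narrow if hospitals differ

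*Protocol*

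**What the plan says.** Section 5.2 (Statistical Methods) names one interval for the accuracy of qLAMP. A ROC curve is built in SPSS 17.0, and "the area under the curve (AUC) and its 95% confidence interval (95% CI) were calculated". R is planned for a model, not specified further, that relates the two tests and derives cut-offs if needed. Neither sentence mentions hospital, and Sections 5.1 and 5.3 do not either.

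The design is multicentre. The Study Summary reports that "21 tertiary hospitals over 14 provinces of P. R. China agreed to participate", and Section 3.3 says "Potential bacterial LRTI patients were consecutively enrolled from 21 tertiary hospitals". Section 5.1 states "We finally plan to enroll 1500 eligible patients" and, for each pathogen, "We estimate the positive rates range 5-15"%. The flowchart in Section 4 places qLAMP, one culture and the serology in a core laboratory, and also shows "Culture in local hospital". It does not say which culture is the reference for the ROC curve.

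**The concern.** Patients from one hospital may resemble each other more than patients from different hospitals. Section 6 accepts spontaneous sputum as well as specimens from bronchoscopy or ventilated patients, and that mix can vary by hospital, as can case mix. If local culture feeds the reference result, its error can vary by hospital too. A pooled ROC interval has no term for any of this.

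Reference-negatives deserve most attention. Each hospital contributes many of them, so a small correlation inflates the variance most there. The Background (Section 1.1) also says that nucleic-acid methods give many more positives than culture in sputum and that this must be explained. The disputed results are therefore mostly index-positive results among culture-negatives. If the clustering is ignored, qLAMP's accuracy could look more certain than data from 21 hospitals allow.

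**Working it through.** **The plan's own figures.** The protocol gives no expected AUC, interval width, specificity or ICC, so there is no figure on this point to reproduce. The nearest is the 400 to 3000 patients in Section 5.1. The formula N = 1.96² × Se(1 − Se) / d² / p, with an assumed half-width d = 0.05, gives:
- 3.8416 × 0.0475 / 0.0025 / 0.15 = 487 (sensitivity 95%, 15% positive)
- 3.8416 × 0.09 / 0.0025 / 0.05 = 2766 (sensitivity 90%, 5% positive)

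This is the same order as the stated range but not a match. No half-width is stated, so the range is not shown to be wrong.

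**Inputs.** From the protocol: 21 hospitals, N = 1500, 5% or 15% positive. Assumed: equal hospital sizes, ICC 0.01 to 0.05, specificity 90%.

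**Patients per hospital, m.**
- 5% positive: 75/21 = 3.6 positives and 1425/21 = 67.9 negatives
- 15% positive: 225/21 = 10.7 positives and 1275/21 = 60.7 negatives

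**Specificity at a cut-off.** Design effect DE = 1 + (m − 1) × ICC. The naive half-width is 1.96 × √(0.9 × 0.1 / n), which is 1.56 points for n = 1425 and 1.65 for n = 1275. Multiply by √DE:

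| ICC | DE, 5% positive | Half-width (points) | DE, 15% positive | Half-width (points) |
|---|---|---|---|---|
| 0.01 | 1.67 | 2.01 | 1.60 | 2.08 |
| 0.02 | 2.34 | 2.38 | 2.19 | 2.44 |
| 0.05 | 4.34 | 3.25 | 3.99 | 3.29 |

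In a beta-binomial simulation (20,000 runs, 5% positive), a naive 95% interval for specificity covered about 87%, 80% and 65% at these three ICCs. If hospital sizes are unequal (assumed coefficient of variation 0.6), the design effects run from 1.82 to 5.56.

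**Sensitivity at a cut-off.** There are few positives per hospital, so the effect is small. At ICC 0.05, DE is 1.13 (5% positive) or 1.49 (15% positive), and the width factor √DE is 1.06 or 1.22.

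**AUC, the planned interval.** This was simulated with 21 hospitals of 71 patients and ICC 0.02 to 0.05. The table shows the true standard error divided by the DeLong standard error that assumes independence, over 5% and 15% positive:

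| How hospital effects act | True AUC 0.85 | True AUC 0.90, equal positive rates |
|---|---|---|
| Shift both groups alike | 1.02–1.03 | 1.00–1.01 |
| Only reference-negatives vary | 1.05–1.19 | 1.04–1.17 |
| The two groups vary separately | 1.07–1.29 | 1.04–1.26 |

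If the positive rate also varies between hospitals (true AUC 0.90), the separate case reaches 1.36 at ICC 0.05. At an ICC of 0.10 the same case reaches 1.64. Naive coverage at AUC 0.85 fell to 86% in the worst setting. At 5% positive, coverage is only about 93% even without clustering, so the ratio of standard errors is the cleaner measure.

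**The case against.** **Independence is not stated.** Section 5.2 names software but no variance method, and the R model is left open. Centre handling is often settled in an analysis plan, which is not at hand. This stands in part: independence is inferred from the named procedure. But the protocol does commit to a specific analysis, and that analysis does not match the design. If an analysis plan already clusters by hospital, the point is closed.

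**No specificity interval is planned.** This stands. A reader might infer from the large design effects that the study's planned specificity intervals are badly wrong. The only specificity in the protocol is the analytical specificity of the primers, so those figures apply only to a clinical specificity interval added at a cut-off.

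**The reference may be central.** This also stands. A reader might infer that the reference is read in 21 laboratories. If the core-laboratory culture is used, then qLAMP, culture and serology are all central, and hospital variation would come only through case mix, sampling and specimen type.

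**The effect on the AUC may be nil.** If hospital effects move both groups together, the ratio is close to 1.0. Nothing in the protocol shows which pattern applies.

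**Hospitals could be treated as fixed.** If inference is confined to these 21 hospitals, variation between them is not sampling error in the same sense. The protocol does not commit to a wider population of hospitals. However, Section 2 frames its objective for LRTI patients in general, which fits the wider reading better.

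**Conclusion.** The analysis in Section 5.2 does not reflect enrolment from 21 hospitals, and its AUC interval would be too narrow if hospitals differ. At an assumed ICC of 0.02 to 0.05, the standard error is understated by a factor of about 1.0 to about 1.3. The upper end needs hospital effects that vary separately in the two groups and 15% positive. A specificity interval reported at a cut-off would have a design effect of about 1.6 to 4.3 at an assumed ICC of 0.01 to 0.05. Its half-width at an assumed 90% specificity would be about 2.0 to 3.3 points rather than 1.6.

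These sizes assume N = 1500 and equal hospitals. The Study Summary instead gives "About 3000 LRTI patients". With 3000 patients and 5% positive, there would be 2850/21 = 135.7 negatives per hospital, and the design effect at ICC 0.01 would be 1 + 134.7 × 0.01 = about 2.3.

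The documents do not support saying that the AUC interval is certainly too narrow: they give no ICC, and an ICC above zero is required. Nor do they support attributing all of the shortfall in AUC coverage at 5% positive to clustering. The point is a cheap improvement, not a defect that undermines the study.

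**What to change.** In Section 5.2, state that the 95% CI for the AUC, and for any sensitivity or specificity reported at a cut-off, is computed in R with hospital as the cluster. Use either a bootstrap that resamples whole hospitals or a cluster-robust variance with a t reference on 20 degrees of freedom (21 hospitals minus 1). Include hospital in the R model relating the two tests. State also whether the core or the local culture is the ROC reference, since this decides whether local laboratory differences enter at all.

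The cost is a few lines of code, and hospital should be known for every patient. Intervals become somewhat wider. With no clustering the price is small: the t multiplier on 20 degrees of freedom is 2.086 against 1.960, or 2.086/1.960 = 1.06 times as wide. In simulation, the cluster-robust interval for the AUC covered 93% to 95% in all the settings tried.

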## Background

Lower respiratory tract infections (LRTI) are a public health problem of major concern, which account for 12% & 16% of the inpatients in city and county hospitals of China. Beyond this, LRTI also importantly contribute to antibiotic overuse and allocation of health resources worldwide. . Many LRTI are caused by organisms that do not require antibiotics or could be safely treatment with narrow-spectrum antibiotics. Identifying the etiology of LRTI by traditional culture test assay needs at least 48-72hr. And there are a large proportion of cases with no pathogen identifying, either because the appropriate tests were not performed or the organism was missed. Thus, treatment of LRTI is generally empirical, with physicians reliant on previous etiology and microbiology studies to guide their choice of intervention, although each of these can be misleading. It is necessary to explore new, rapid and accurate diagnostic techniques.

A PCR-Chip assay for sepsis named prove-itTM was approved in Finland, which detects 31 pathogen bacteria in 3hours. But this non-quantitative method only work with blood or body fluid normally asepsis, while not sputum, the most convenient and routine specimen of LRTI, as many other similar methods . Real-time PCR, NASBA, LAMP, and many quantitative nuclear acid amplification methods had been successively applied in clinical virus detection, such as CMV, HCV, HBV, HIV. And some of these methods had been approved to be able to detect several pathogens simultaneously with perfect sensitivity and specificity in standard bacteria stains. While in the term of bacteria or fungi, these methods showed much more positive results in clinical sputum sample tests according to traditional culture assay. The discrepancies must be rationally explained before these methods to be applied in clinical.

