## Preclinical Data

Genomic sequences of 11 bacteria species, i.e. *Acinetobacter baumannii, Escherichia coli, Haemophilus influenzae, Klebsiella pneumoniae, Pseudomonas aeruginosa, Staphylococcus aureus, Stenotrophomonas maltophilia, Streptococcus pneumoniae*, *Legionella pneumophila, Mycoplasma pneumoniae* and *Chlamydophila pneumoniae* were retrieved from Genebank. Each primer set was designed based on the strategy described previously, and sensitivity, specificity and reproducibility of them were evaluated by quantified DNA from 27 species of bacteria. Quantitative LAMP assay was performed by real-time fluorescence detection modified from a previously published protocol.

Quantified DNA of the 11 tested bacteria, which was extracted and purified by QIAamp according to the manufacturer’s instructions, was serially diluted as positive control. Concentration of copy-number of genomic equivalents was calculated based on its genome size to plot standard curve. Then the equivalent copy numbers of the template DNA were determined based on the standard curves generated from quantified control DNA.

The sensitivity of each set of primers was determined by serially diluted each targeted DNA template as the consistently detectable minimal content (copies/μl DNA template), then traced to the titer of bacteria in sputum by the following equation:

Titer in sputum [copies/ml] = copies/μl (content in DNA template) × 100μl (template volume) / 0.5 ml (sputum volume)

The specificity of each set of primers were evaluated by quantified bacteria DNA of 27 species (8 targeted and 19 reference species, listed in Supplement Table 4) obtained as mentioned above, to exclude primer set show any cross reaction with other species DNA.

Serially diluted each targeted DNA templates were tested at least 8 times at different time and on different machines. The ranges of error were calculated to evaluate the reproducibility of our LAMP system.

Our primer sets for the 11 bacteria showed sensitivities to a titer of 103copies/ml in sputa and specificities where no detectable cross-reaction with DNA from 26 other bacterial species. The maximum range of titer from single standard DNA temple was less than 6 fold. These showed acceptable sensitivity, specificity and reproducibility of our LAMP system.

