# Study Objectives

Primary Objective

To compare and determine the etiology diagnostic test accuracy of qLAMP test and routine bacteria culture/serological test for the etiology diagnosis in LRTI patients with sputum samples.

Secondary Objective

1. To compare results of qLAMP with the results of routine culture/serological test, or

Assess the relationship between the results of qLAMP and routine bacterial culture/serological test.

2. To evaluate the necessity of quantization and cut-off setting.

3. To explore heterogeneity in term of bacterial pathogens involved in LRTI.

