## Subject Population(s) for Analysis

the subject populations whose data will be subjected to the study analysis is the population, in which any subject who was randomized and had qualified samples and clinical informations.

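### Cut-offs derived from the study data, with no separate validation described, would overstate sensitivity by about 1 to 3 points on the protocol's own planning figures; the AUC is unaffected

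*Protocol*

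**What the plan says.** The protocol fixes no clinical qLAMP cut-off for any of the 11 bacteria. Section 5.2 (Statistical Methods) gives two analyses. The first is an ROC curve for which "the area under the curve (AUC) and its 95% confidence interval (95% CI) were calculated". The second is exploratory: "R software will be used to construct statistical model to explore to relationship between the result of both tests, and calculate cut-offs if necessary".

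Cut-offs are also a study question. Secondary objective 2 in Section 2 is: "To evaluate the necessity of quantization and cut-off setting". Section 1.1 (Background) suggests why one may be needed. For bacteria and fungi, it says, "these methods showed much more positive results in clinical sputum sample tests according to traditional culture assay".

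The only titre given in advance is analytical. Section 1.3 (Preclinical Data) reports: "Our primer sets for the 11 bacteria showed sensitivities to a titer of 103copies/ml in sputa" (10^3, with the superscript lost in the text). Section 5.3 defines a single analysis population, "any subject who was randomized and had qualified samples and clinical informations". Section 5.1 supplies the planning values: "We estimate the positive rates range 5-15%, and the sensitivity of the index qLAMP test is 90- 95" per cent, with 1500 eligible patients planned.

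**The concern.** Section 5.2 leaves both the decision to use a cut-off and its value to the study data, and only one set of patients is described. A threshold picked because it performs well in a sample partly fits the noise in that sample, so its apparent performance there exceeds its performance in new patients. The fewer the reference positives, the larger the excess. Up to 11 cut-offs could be chosen this way.

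Two results are at stake: the sensitivity quoted at each derived cut-off, and the answer to secondary objective 2. The second has a structural problem. If the cut-off maximises an index over all thresholds, and the detection limit is one of those thresholds, the cut-off cannot score below the detection limit on that index in the same patients. An uncorrected comparison could then never come out against cut-offs, even if they add nothing.

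**Working it through.** **The plan's own figure.** The protocol gives no figure for optimism. Its related figure is the 400-3000 patients in Section 5.1. The usual precision formula is N = z² × Se × (1 − Se) / (d² × prevalence), with two-sided z = 1.96. The half-width d is not stated. With d = 0.05:

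- Se 95%, 15% positive: 3.8416 × 0.0475 / (0.0025 × 0.15) = 487
- Se 90%, 5% positive: 3.8416 × 0.09 / (0.0025 × 0.05) = 2766

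This is the same order as 400-3000 but not a match. With d unstated and the range apparently rounded, I do not call it an error. It does indicate that sensitivity was the quantity planned for.

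**Inputs from the protocol.** N = 1500 eligible; positive rate 5-15%, so 1500 × 0.05 = 75 to 1500 × 0.15 = 225 positives per pathogen; sensitivity 90-95%.

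**Assumptions, not in the protocol.** Titres are normal with equal variance in positives and negatives. Specificity equals sensitivity at the ideal cut-off, so the separation is 2 × Φ⁻¹(Se), giving an AUC of about 0.965 (Se 90%) or 0.990 (Se 95%). The selection rule is either the maximum Youden index or the highest cut-off with apparent sensitivity of at least 90%.

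**Calculation.** Optimism = apparent sensitivity minus true sensitivity at the chosen cut-off, averaged over 2000 simulated studies (Youden) or 1000 (the 90% rule). The half-width is 1.96 × √(Se(1 − Se)/positives). All entries are percentage points, shown for Se 90% / 95%.

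| Positive rate | Positives | Youden | Sensitivity ≥ 90% rule | 95% CI half-width |
|---|---|---|---|---|
| 15% | 225 | +1.4 / +1.0 | +0.3 / +0.4 | 3.9 / 2.8 |
| 10% | 150 | +1.8 / +1.4 | +0.4 / +0.6 | 4.8 / 3.5 |
| 5% | 75 | +2.8 / +2.1 | +1.1 / +1.1 | 6.8 / 4.9 |
| 2% (assumed) | 30 | +5.0 / +4.3 | +2.8 / +2.8 | 10.7 / 7.8 |
| 1% (assumed) | 15 | +7.8 / +6.6 | +5.9 / +5.9 | 15.2 / 11.0 |

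Specificity changes by 0.2 points or less throughout, because negatives are many.

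**Weaker separation.** With an AUC of 0.85, the Youden index (sensitivity + specificity − 1) is overstated by 2.7 points with 150 positives, 4.0 with 75, 6.9 with 30 and 10.3 with 15, nearly all of it in sensitivity. In this model an AUC of 0.85 means about 77% sensitivity at the ideal cut-off, well under the protocol's 90-95%, so these figures are a stress case.

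**The comparison with simple detection.** Let J(c) be the index in the sample at threshold c, and let the chosen cut-off maximise J. Then J(chosen) ≥ J(detection limit) in every data set. This needs no assumption about prevalence or titre distribution, only that the rule maximises the index on which the comparison is made.

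**The case against.** The strongest objection is that cut-off rules and internal validation are commonly left to the SAP, which is not shown. The protocol does not say that accuracy at a derived cut-off will be reported uncorrected, nor in words that the same patients serve both purposes. This stands as a limit on certainty: shared patients are inferred from the single population and the lack of any other. It does not remove the point, because Section 5.2 itself makes the cut-off depend on the data and Section 2 makes the need for one an objective.

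Second, the named accuracy measure is the AUC, which choosing a cut-off does not bias. This stands in full. A reader might infer that the protocol's main accuracy result is compromised, and the text does not support that. But the AUC alone cannot answer objective 2.

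Third, the effect is small. Within the protocol's own ranges the mean bias is below the 95% CI half-width in every row, and smaller still under the 90% rule. This stands too, although an ordinary interval centred on an inflated estimate does not remove a bias that runs the same way for every pathogen.

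A reader might also infer overstatements of 7 to 10 points for the rarer pathogens, or that the sensitivities will fail in new patients. Such sizes need positive rates of about 1-2%, some of them also a separation below the planned one. Section 5.1 admits that accurate positive rates are lacking, so low rates are possible, but no figure in the protocol supports them.

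**Conclusion.** The point holds as a cheap improvement. If derived cut-offs are assessed in the patients who produced them, sensitivity at those cut-offs and the objective 2 comparison will be optimistic. On the protocol's own figures the mean overstatement of sensitivity is about 1 to 3 points under Youden and about 0.3 to 1.1 points under a rule requiring at least 90% sensitivity, against a planning range for sensitivity only 5 points wide. Almost none of it is in specificity, and the AUC is untouched. The direction, and the increase as positives become fewer, appear under both rules. The size rests on the assumed rule and titre distribution, neither of which the protocol states. Whether the bias would change the answer to objective 2 cannot be determined, because the protocol gives no expected accuracy at the detection limit in patients.

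**What to change.** Add a short paragraph to Section 5.2, or to the SAP if it does not already cover this:

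- For every pathogen where a cut-off is derived, state the selection rule and repeat the whole selection inside a bootstrap or cross-validation, including the decision whether a cut-off is needed.
- Report the optimism-corrected sensitivity and specificity beside the result at the stated detection limit of 10^3 copies/ml. Treat that limit as a fixed comparator, not as a proposed diagnostic threshold.
- Judge secondary objective 2 on the corrected difference between the two.
- Label uncorrected values at derived cut-offs as exploratory.

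Resampling is preferable to setting centres aside: 75 positives over 21 hospitals is about 3.6 per centre (75 / 21), so a split by centre would be imprecise. No extra patients or samples are needed. The cost is a little more analysis and slightly lower reported sensitivities. Where positives are very few, the corrected value will itself be imprecise and should be shown with its uncertainty.
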